#### 2.8.2. Data Management

Personal information obtained in this study will be coded and anonymized.

All the data for the present study will be managed securely for 5 years from completion. All materials will be disposed of after this period, and sufficient care will be taken to ensure that the names of individuals on the signed informed consent forms cannot be identified.

#### 2.8.3. Criteria for Discontinuation of Participation in the Study or of the Study

If a participant withdraws consent for participation in the study.If their physician determines that the continuation of the intervention is not preferable for an individual patient. At the moment, there is no reason that can be used to exclude a patient from the trial apart from the aforementioned exclusion criteria, which might minimize bias affecting the results of the study.If the study protocol cannot be followed.

### 2.9. Monitoring

Information about the initiation of the study, the conduct of the study, ethical considerations, the occurrence of detrimental or adverse events, the results of the study, and registration of the study with a public database will be submitted to our ethics committee.

#### 2.9.1. Protocol Amendments

If any amendments are made, the Ethics Committee will be notified.

#### 2.9.2. Follow-Up of Adverse Events

This study involves the implementation of a lifestyle program focused on a healthy diet and exercise to help persons with prediabetes reduce their risks to develop type-2 diabetes.

There is little likelihood of any health hazards. If any serious adverse events do occur, they will be reported in line with the standard operating procedure for Reporting Serious Adverse Events in Clinical Research.

### 2.10. Ethics and Dissemination

The study is implemented in accordance with the Declaration of Helsinki and the ethical guidelines for medical research covering humans. This study has been approved by the Ethical Committee of Extremadura University (No.165//2021). No information identifying specific patients is stored alongside study data. Only the authors will have access to the final trial dataset. It is considered that harm to the patient will be rare because the examinations performed will be those undertaken in the usual medical examination. However, participants will freely exit the study if they want to.

## 3. Discussion

The striking increase in the incidence of type-2 diabetes mellitus and its broad consequences has led us to focus on preventing its development through educational interventions that reduce the associated risk regarding lifestyle choices [22,23,24,25].

However, studies in our target population are scarce mostly due to lower incidence compared with other age ranges. Notwithstanding that fact, given the chronic character that diabetes mellitus has, it is paramount to prevent its development at any age range. As a result, we chose to run a parallel-comparison trial so every patient—regardless of their allocation in the study—will be aware of their pre-diabetic status and make evidence-based and healthy changes in their lifestyle.

COVID-19 has strained and changed the healthcare system during these past two years, being a priority over chronic diseases [42]. Furthermore, both group and individual interventions onsite were suspended. However, telemedicine has increased and developed greatly, becoming an effective tool to deliver educational interventions. There have been research studies prior to and during COVID-19 that have proven the efficacy of online educational interventions [27,28,29]. As a result, these interventions have the potential to bridge the gap between the limited supply of healthcare resources and the growing demand for diabetes education.

There are several potential limitations of the planned study. First, the assessment of body weight changes from baseline to 6 months might reflect only those changes occurred in the short term. This will be taken into account in further research. Nonetheless, several studies have set up 6 months to collect endpoint assessments [28,31].

Second, even though all university staff will be included in the study, that is, low, middle and high educational status population, given the highest high-educational status population rate, the low and middle-educational status population might be underrepresented.

Third, by carrying out a parallel-comparison trial with two intervention groups, we expect changes in both groups. However, our study will assess whether follow-up and motivation are needed in achieving lifestyle changes, providing a viewpoint that could help healthcare professionals manage their workload more efficiently.

As a consequence, we expect to find an improvement leveling off those T2MD risk factors in the pre-diabetic population aged 18–45 years old, hypothesizing that follow-up and motivation are needed to achieve lifestyle changes when using online educational intervention focused on improving diet and exercise lifestyle choices.

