The study hypothesis is that online educational intervention focused on lifestyle changes is effective in reducing body weight when engaging activities are encouraged and present throughout the first weeks of behavioral modifications.

The aim of the study is to analyze the efficacy of an online educational intervention focused on lifestyle changes in reducing body weight from baseline to 1 and 6 months in the pre-diabetic population of 18–45 years old in Extremadura (Spain).

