## 2. Materials and Methods

### 2.1. Study Design and Settings

The study is a single-blind, multicenter randomized parallel-comparison trial with two intervention groups in a 1:1 ratio. Participants were blinded to the allocated group, but researchers performing the intervention were not.

The trial registration code is 10.17605/OSF.IO/4D8FJ and was designed so that it can be reported according to the SPIRIT 2013 statement [30]. The study will be carried out across three centers of the University of Extremadura (UEx).

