### 2.6. Intervention

Both groups will be separately summoned to receive details about the intervention protocol in a welcome synchronous session at the university.

Participants allocated to the intervention-A group will have been provided access to information about healthy diet and exercise through the university’s online campus, to help them implement long-term changes in their diet and exercise habits using videos, recorded classes, and online information. A reminder of the following measurement appointment in one month will be sent and then for the 6 months final data collection. This intervention group will not be encouraged or motivated by the researchers but rather informed of their status and recommended to implement healthy diet and exercise habits.

Participants allocated to the intervention B group will have been provided with a six-session educational program mixing synchronous and asynchronous methodology concerning educational and behavioral changes regarding diet and exercise habits. All sessions will be carried out on the university’s online campus in one month so participants can promptly implement their exercise routines and diet changes through several proposed activities that they should complete. The first month of lifestyle treatment is a critical period for helping participants achieve weight loss according to the results of Miller et al. [41].

Participants will be assigned a personal trainer to make follow-ups and provide personal motivation. This activity will be held by two clinical nurse researchers who are trained in motivating patients. There will be constant feedback regarding the process and possible distractors via mail, telephone, or videoconference in order to surge adherence to the intervention.

Each session will have 2 h duration and pivot on three main issues: diet, exercise, and motivation, which according to Zhang et al. have been proven to be the central issues to work on [29]. Using synchronous methods will help promote participant retention and complete follow-up.

The first session, named “walking toward a healthy diet”, will be dedicated to identifying those fatty and sugary foods (both hidden and naturally present) and explaining strategies to avoid them by interchanging them for healthier options.

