It will also help participants acknowledge sources of stress linked to binge eating and provide them with some strategies according to the scores in the questionnaires. Furthermore, participants will learn about type-2 diabetes through an educational video created by nurse researchers.

After this session, participants will begin to register their fruits and vegetables and high fat and sugar food intake in a diary. Furthermore, they will try to identify barriers and stressors to a healthy diet.

In the second session, named “give exercise the value that it has”, we will focus on explaining the benefits of exercising, showing participants easy ways of exercising, and how to improve exercise adherence using motivation.

After this session, participants will begin to implement strength and aerobic exercise in their routine and register it using fitness tracker wristbands.

Session three, named “barriers and stressors that block me from implementing a healthy diet”, will be a synchronous group session focused on those found barriers and stressors to maintaining a healthy diet and designing a plan to tackle them. After this session, participants will implement the plan and register any digression.

Session four, named “get up and get moving”, will help reinforce exercise habits and give participants the option to discuss any encountered limitations, their best exercise hours, and exercise planning. After this session, participants will further implement their exercise plan.

Session five, named “dealing with our surroundings I”, will be a synchronous group session focused on a real-life testimonial speech from a young diabetic person who will discuss what it feels like to deal with type-2-diabetes at a young age. A colloquial will be initiated after the speech for every participant to ask or discuss any issue. Additionally, participants will be asked to share a healthy picnic with friends or family and post photos on the online campus. Another option will be to post on the online campus a video of themselves preparing a healthy meal. The purposes will be overcoming negative social signals related to food and being able to make healthy decisions regarding “eating outside”.

Session six, named “dealing with our surroundings II”, will be an asynchronous session showing Spanish influencers who promote healthy diets and exercises. After the session, participants will share photos of themselves practicing any exercise.

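### The two-arm contrast tests a whole programme, so it cannot answer the Discussion's question about the need for follow-up and motivation

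*Protocol article*

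**What the plan says.** Section 2.1 describes a "parallel-comparison trial with two intervention groups in a 1:1 ratio". Section 2.6 sets out what each arm receives.

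- **Arm A** has access to diet and exercise material on the online campus, "using videos, recorded classes, and online information". It gets reminders of the measurement visits, and the researchers are not to encourage or motivate it.
- **Arm B** "will have been provided with a six-session educational program mixing synchronous and asynchronous methodology". Each session lasts 2 hours, and the themes are diet, exercise and motivation. A personal trainer gives follow-up, motivation and feedback. Participants keep a food diary, and for their exercise they "register it using fitness tracker wristbands". There are also group sessions, a plan against personal barriers, a talk by a young person with diabetes, and tasks such as posting photos or a cooking video.

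Section 3 (Discussion) says of this design that "our study will assess whether follow-up and motivation are needed in achieving lifestyle changes", and offers the answer as help for professionals in managing their workload. The last paragraph repeats the idea as a hypothesis: "hypothesizing that follow-up and motivation are needed to achieve lifestyle changes when using online educational intervention". The three stated limitations are short follow-up, under-representation of lower educational levels, and expected change in both arms.

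**The concern.** The question in the Discussion is about named components. The randomisation is between two packages that differ in those components and in several others at once. If arm B loses more weight, the cause could be the trainer's follow-up, the structured teaching, self-monitoring by diary and wristband, peer contact, total contact time, or a combination.

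This matters because the component claim comes with a practical use, the allocation of professional time. A reader who takes it at face value could put staff time into follow-up and motivation when another part of the programme was responsible. The word *needed* also asks for more than a difference between arms can give.

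**Working it through.** **Step 1: the arms side by side (section 2.6).** A dash means that the article describes the element only for the other arm.

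| Element | Arm A | Arm B |
|---|---|---|
| Online diet and exercise content | videos, classes, information | taught within the sessions |
| Structured sessions | – | 6 × 2 h = 12 h |
| Trainer follow-up, motivation, feedback | – (encouragement explicitly withheld) | yes |
| Food diary | – | yes |
| Fitness wristband | – | yes |
| Group plan against barriers | – | yes |
| Testimonial with discussion | – | yes |
| Picnic, photo or video tasks | – | yes |

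**Step 2: what the contrast identifies.** Let F be the effect of follow-up and motivation, S the effect of everything else that arm B adds, and I their interaction. The mean difference is

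B − A = F + S + I.

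That is one estimable quantity and three unknowns. To separate F, the trial would need an arm with S but without F, or one with F but without S. With two arms there is neither. No analysis plan can supply the missing contrast, because the limit lies in the arms.

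**Step 3: whether a difference would show need.** Showing that F is needed for lifestyle change would require evidence that change does not occur without it. The Discussion itself expects change in both arms, including arm A, which is not encouraged. If that happens and B does better than A, the finding is added benefit from a package, not necessity of one part of it.

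**Step 4: whether the sample size is affected.** Section 2.3 gives SD 14 kg, correlation 0.9, a 4 kg difference, two-sided 0.05 and 80% power, for 37 per group.

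- Baseline-adjusted SD = 14 × √(1 − 0.9²) = 6.10 kg.
- n per group = 2 × (1.960 + 0.842)² × 6.10² / 4² = 36.5, rounded up to 37, or 74 in total. Power at 37 per group is 80.5% (normal approximation).
- With an unadjusted change score, SD = 14 × √(2 × 0.1) = 6.26 kg and n = 39 per group. Power at 37 per group is then 78.5%.

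The stated 74 reproduces with baseline adjustment. It is the sample size for the whole B − A difference of 4 kg, which is the question the trial can answer.

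**Step 5: whether the limitations cover it.** None of the three mentions that the arms differ in several elements. The component claim is offered as the counterweight to the third, the expected change in both arms.

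**The case against.** **The phrase may be shorthand.** The article uses follow-up and motivation broadly. The abstract speaks of follow-up activities in arm B, motivation is one of the three session themes, and section 2.6 links synchronous teaching with retention and complete follow-up. The diary, testimonial and photo tasks could be counted under the same label. This has some force, but the structured diet and exercise teaching and the wristbands fall outside even that broad reading. The attribution problem becomes smaller but does not go away.

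**The design is legitimate.** Comparing a multicomponent programme with minimal information is a sound pragmatic question. That stands: the fault is in the interpretation, not in the randomised comparison.

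**Stronger readings that the article does not support.**

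- A reader might infer that the authors have committed to a conclusion. The text says only that the study will assess and that they hypothesise, and the Methods contain no rule for drawing such a conclusion.
- A reader might infer that the Introduction's hypothesis, that "online educational intervention focused on lifestyle changes is effective in reducing body weight", goes untested because no arm is untreated. The sentence continues by making this conditional on engaging activities being encouraged in the early weeks. Read in full, it fits the package contrast reasonably well. The Discussion also explains why every participant receives something.
- A reader might infer that the two arms share no teaching content. Arm A's material is not itemised in this article, so the overlap cannot be judged.
- A reader might put the share due to follow-up and motivation at anywhere from 0% to 100%. That is not a calculation, and it is not even a bound if components interact or offset each other.

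**Conclusion.** The point holds for the two statements in the Discussion. The A–B contrast can show whether the arm B programme as a whole does better than online information alone. It cannot attribute a difference to follow-up and motivation or show that they are necessary, and the listed limitations do not acknowledge this.

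The size can be described but not calculated: 12 hours of sessions and at least five other elements (diary, wristband, barrier plan, testimonial, sharing tasks) change together with trainer follow-up, and the separate contribution is not identifiable. The conclusion assumes that the elements described only for arm B are in fact given only to arm B. It does not depend on how much teaching content the arms share. Allocation, endpoint and sample size stand, and the Introduction's hypothesis needs no change on this ground.

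**What to change.** Reword the two statements in section 3 to the randomised question: whether the arm B programme as a whole gives greater weight loss at 6 months, the time point of the power calculation, than online information alone. Add that:

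1. any effect is attributed to the package, and no separate conclusion will be drawn on follow-up or motivation;
2. changes within either arm are descriptive, since there is no untreated comparator;
3. the bundling of components in arm B is a limitation, listed with the other three.

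This changes wording only. Arms, sample size, visits and data collection stay as they are. The cost is a narrower claim than the authors planned, in particular on how professionals should use their time. Isolating follow-up and motivation would take a different design, with arms that share the other components.

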## Figures and Tables

**Figure 1 jpm-12-01669-f001:**
[figure not shown]
Participant flow diagram.
